**Inclusion criteria**
Acute ischemic stroke confirmed by head CT or MRI
Female or male patient aged ≥18 years and ≤80 years
Time from symptom onset to the randomization ≤72 h
4 ≤ NIHSS score ≤16 (total score of upper and lower limbs on motor deficits ≥2) at the randomization time
Signed informed consent

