### Efficacy Outcomes

In this trial, the primary outcome is neurological deficit amelioration defined as a change in the NIHSS score from baseline to 10 post-randomization days. Secondary outcomes will be as follows: 1) the proportion of patients with early neurological improvement (NIHSS score 0–1) at 10 post-randomization days; 2) patients’ subjective feelings measured at 10 post-randomization days using the Patient-Reported Outcomes scale for Stroke (PRO-Stroke), which is a well-validated scale suitable in Chinese patients for assessing stroke and treatment effects on physical function, psychological change, social engagement, and treatment satisfaction (Wang et al., 2012a; Wang et al., 2012b; Wang et al., 2012c); 3) proportion of patients with life independence (90-days modified Rankin Scale [mRS] score ≤1); 4) proportion of patients with a favorable outcome (90 days BI score ≥90); and 5) patients’ quality of life measured using the Stroke-Specific Quality of Life (SS-QOL) at 90 days.

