### Sample Size Calculations

Based on a previous study that reported a mean decrease in the NIHSS score of 3 and 2.1 in the PNS and control groups, respectively, and a standard deviation of 2.5 (Wang, 2009), this trial will require 480 patients with a power of 90%, two-sided α of 0.05, and a 20% dropout rate to test the hypothesis that PNS is superior to placebo in decreasing the NIHSS score at 10 post-randomization days in patients with AIS.

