### Statistical Analysis Plan

All randomized patients who receive at least one treatment dose and have safety outcome data will be included in the safety set. All patients in the safety set will be included in the full analysis set if efficacy outcome data are available. All patients in the full analysis set who are deemed to have no major protocol violations will be included in the per-protocol set. Efficacy and safety analyses will be performed according to the intention-to-treat principle. Additionally, per-protocol data analysis will be conducted as a reference. The last observation carried forward approach will be used to impute missing data of primary outcome. Regarding the primary outcome variable, between-group comparisons of the change in NIHSS score will be performed using Student’s *t*-test or Mann-Whitney *U* test, as appropriate. Regarding secondary outcome variables, between-group comparisons of the proportion of patients with an NIHSS score of 0–1, mRS grade ≤1, and BI score ≥90 will be performed using the chi-square test or Fisher exact test. Further between-group comparisons of the PRO-Stroke and SS-QOL score, as well as changes in biological indexes, will be compared using the *t*-test or Mann-Whitney *U* test. Moreover, between-group comparisons of the incidence of AEs will be compared using the chi-square or Fisher exact test. The effect of missing data on the results will be assessed through sensitivity analysis. All statistics will be 2-sided and statistical significance will be set at *p* < 0.05. Statistical analyses will be performed using SAS software version 9.4 (SAS Institute Inc.).

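### The primary comparison of NIHSS change is valid but leaves out baseline NIHSS and centre; a single prespecified ANCOVA would give more precision at no cost

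*Protocol article*

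**What the plan says.** Under Efficacy Outcomes, "the primary outcome is neurological deficit amelioration defined as a change in the NIHSS score from baseline to 10 post-randomization days". The Statistical Analysis Plan section then states that "between-group comparisons of the change in NIHSS score will be performed using" a t-test or a Mann-Whitney test, whichever is judged suitable. It names no covariate, no adjusted model and no rule for choosing between the two tests.

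Four other places bear on this:

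- **Table 1, inclusion criteria:** patients enter with "4 ≤ NIHSS score ≤16 (total score of upper and lower limbs on motor deficits ≥2) at the randomization time", so severity varies widely at entry.
- **Follow-Up Procedures:** NIHSS is assessed at the baseline visit.
- **Randomization, Allocation, and Blinding:** allocation is 1:1 in blocks, stratified by centre only.
- **Subgroup Analyses:** baseline severity appears as a subgroup factor for the primary outcome, but not in the primary comparison itself.

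**The concern.** Subtracting baseline does not make the change score independent of baseline. A patient who enters at 4 can improve by at most 4 points, whereas one who enters at 16 has far more room. If change is correlated with baseline NIHSS, part of its variance is predictable from a measurement already in hand, and an unadjusted test leaves that part in the error term.

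Randomization does not balance severity by design, so the arms can differ in baseline NIHSS by chance. An unadjusted estimate carries the consequence. If such an imbalance is noticed only after unblinding, adjusting for it then would be post hoc.

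The two named tests also target different quantities. The trial was sized on a difference in mean change, which a Mann-Whitney test does not estimate. Naming one model would settle which quantity is primary.

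**Working it through.** **Inputs from the document (Sample Size Calculations).** "mean decrease in the NIHSS score of 3 and 2.1 in the PNS and control groups" gives a difference of 3 − 2.1 = 0.9 points. The other inputs are "a standard deviation of 2.5" (read here as the SD of the change), "two-sided α of 0.05", 90% power, 20% dropout and 480 patients.

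**The plan's own figure.** With the normal approximation, n per arm = 2 × (1.960 + 1.282)² × 2.5² / 0.9² = 162.2, so 163 per arm and 326 in total. Dividing by 0.8 gives 408. The stated 480 is not reproduced, but it errs on the large side. That is a separate matter and this point does not depend on it.

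**Power of the stated t-test.** Evaluable per arm: 480 × 0.8 / 2 = 192. The standard error is 2.5 × √(2/192) = 0.255 and 0.9 / 0.255 = 3.53. Noncentral-t power is 94.0%.

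**Assumed inputs, not in the document.** Baseline SD of 3.2 and a slope of change on baseline of 0.2 to 0.3. Then r = slope × baseline SD / SD of change:

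- slope 0.2: 0.2 × 3.2 / 2.5 = 0.26
- slope 0.3: 0.3 × 3.2 / 2.5 = 0.38

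**Effect of ANCOVA.** The residual SD is 2.5 × √(1 − r²), and the variance falls by r².

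| r | Variance reduction | Residual SD | Power at 192 per arm |
|---|---|---|---|
| 0 | 0% | 2.50 | 94.0% |
| 0.26 | 7% | 2.41 | 95.4% |
| 0.38 | 14–15% | 2.31 | 96.8% |

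(At r = 0.38 the reduction is 14.4%; at the unrounded 0.384 it is 14.7%.) At r = 0 the only cost is degrees of freedom: one for baseline and ten for 11 centres, out of 382.

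**Chance imbalance, same assumptions.** The 95% limit of the baseline difference at 192 per arm is 1.96 × 3.2 × √(2/192) = 0.64 points. Multiplied by the slope, it moves the unadjusted estimate by 0.2 × 0.64 = 0.13 to 0.3 × 0.64 = 0.19 points, or 14% to 21% of the 0.9-point target. This is the limit, not the typical case: at slope 0.3 the median absolute shift is 0.674 × 0.327 × 0.3 = 0.07 points.

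**Centre.** The document gives no between-centre variance, so no gain from adding centre is claimed here.

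**The case against.** The strongest reply is that nothing here is broken. Under randomization an unadjusted comparison of change scores is unbiased and controls type I error. Its standard error already allows for chance imbalance in severity, and the planned 90% power is exceeded without adjustment. All of that stands. The linear model is also an approximation on a bounded integer scale, and ANCOVA removes only the linear effect of imbalance in baseline NIHSS, not imbalance in general. Both stand too; the first is a reason for robust standard errors.

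Three stronger readings are tempting, and the document does not support them.

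- **That the test may be picked by its result.** A reader might infer this from the open choice between two tests. The ordinary meaning is a choice by distribution. Data analysts are blinded until the codes are opened, and analysis lies with a third-party statistical unit. In 8,000 simulated trials at 192 per arm, choosing by a normality pre-test kept type I error near 0.05. Only reporting the smaller p-value raised it, to 0.059–0.073, and nothing in the text says that this will be done. The switching criterion may well be in the full protocol or SAP.
- **That the trial could end with no estimate in NIHSS points.** A Mann-Whitney p-value does not prevent a mean difference from being reported.
- **That the gain is large.** At r = 0.5 the variance reduction would be 25% and power 98.2%, but a slope of 0.2 to 0.3 with the SDs used above does not reach that correlation.

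An unseen SAP might also specify an adjusted model. The article, however, does not leave the primary analysis open to that: it names two unadjusted tests.

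**Conclusion.** The point holds as a free improvement. The stated primary analysis is valid and adequately powered on the document's own figures, but it ignores the most obvious prognostic covariate and the stratification factor. The expected gain is modest: about 7% to 15% less variance, and 1.4 to 2.8 percentage points of power at 192 per arm. There is also protection against a shift of up to about 0.13 to 0.19 points at the 95% limit of baseline imbalance.

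These sizes rest on an assumed baseline SD of 3.2, an assumed slope of 0.2 to 0.3, and on reading 2.5 as the SD of the change. The document fixes neither of the first two, so the gain could be smaller or larger. The direction does not depend on them: in a trial of this size, adjustment is at least as precise as no adjustment, and at r = 0 it costs essentially nothing.

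**What to change.** Before unblinding, replace the choice of two tests by one primary model: ANCOVA of NIHSS change at day 10 on treatment, baseline NIHSS as a continuous covariate, and centre, with robust standard errors. Using day-10 NIHSS as the response gives the same treatment coefficient. Report the adjusted mean difference in NIHSS points with its 95% confidence interval, so that the result is on the scale of the planned 0.9-point effect. Keep the rank-based test as a named sensitivity analysis.

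The cost is a change of wording in the analysis section. No new data, visits or patients are needed, because baseline NIHSS and centre are already recorded.

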### Randomization, Allocation, and Blinding

The investigators will randomize 480 eligible patients and assign them to the intervention and control groups at a 1:1 ratio using block randomization with stratification according to medical centers. The randomization schedule will be generated by an independent statistician using SAS software version 9.4 (SAS Institute Inc.) and kept in sealed, sequentially numbered, opaque envelopes. Investigational medicine blinding will be completed at a pharmaceutical factory based on the randomization schedule and sent to medical centers along with the emergency envelopes. The block size will be closed to ensure concealment throughout the entire trial period. All investigators, participants, caregivers, and data analysts will be blinded to the treatment assignments throughout the trial until the blind codes are unconcealed. Investigators can request emergency unblinding in case of serious adverse events (SAEs) suspected to be associated with investigational medicine. Figure 1 presents a flowchart of the EXPECT trial.

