### Biological Outcomes

We will perform between-group comparisons of the changes in ICAM-1, IL-6, TNF-α, and MMP-9 levels from baseline to 10 post-randomization days.

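### The secondary binary outcomes and the biomarkers are tested without the baseline values that the trial collects; the tests are valid, but precision may be lost

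*Protocol article*

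**What the plan says.** Everything here is from the protocol article.

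- **Outcomes.** Efficacy Outcomes lists "the proportion of patients with early neurological improvement (NIHSS score 0–1) at 10 post-randomization days", 90-day mRS of 1 or less, 90-day BI of 90 or more, PRO-Stroke and SS-QOL. Biological Outcomes adds: "We will perform between-group comparisons of the changes in ICAM-1, IL-6, TNF-α, and MMP-9 levels", from baseline to day 10.
- **Tests.** In Statistical Analysis Plan the comparison of NIHSS 0–1, "mRS grade ≤1, and BI score ≥90 will be performed using the chi-square test or Fisher exact test". PRO-Stroke, SS-QOL and the biomarker changes get a t-test or Mann-Whitney test. No covariate is named for any of them.
- **Baseline data.** Table 1 admits NIHSS 4 to 16. Follow-Up Procedures has NIHSS and biological samples taken at baseline and again at day 10.
- **Control of severity by design.** Allocation is "at a 1:1 ratio using block randomization with stratification according to medical centers"; severity is not a stratification factor.
- **Use of severity in analysis.** It appears only under Subgroup Analyses, and only for the primary outcome.

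**The concern.** NIHSS 0–1 is a fixed threshold applied to patients who start at very different distances from it. Someone entering at 4 needs a gain of 3 points; someone entering at 12 needs 11. A chi-square test treats these patients as exchangeable and leaves the spread in baseline severity as noise. To some degree the same may apply to mRS 0–1 and BI of 90 or more.

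For the biomarkers, subtracting the baseline is not the same as regressing on it. A change score stays correlated with the baseline level unless the regression slope of day 10 on baseline is 1, so some removable variance remains.

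At stake is power for outcomes that the trial was not sized for, and a treatment estimate that moves with whatever chance difference in severity the two arms happen to have. The data needed to do better are already in the case report form, but the covariates must be fixed before unblinding to be credible.

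**Working it through.** **1. The plan's own figure.** Sample Size Calculations gives a "mean decrease in the NIHSS score of 3 and 2.1 in the PNS and control groups, respectively", "a standard deviation of 2.5", and "power of 90%, two-sided α of 0.05, and a 20% dropout rate", and concludes that "this trial will require 480 patients". With n = 2(1.96 + 1.282)² × 2.5² / 0.9², n is 163 per arm, 326 in total, and 326/0.8 = 408 with dropout. The stated 480 is therefore larger than its inputs require. That concerns the primary outcome and does not bear on this point. No figure is given for any secondary or biomarker outcome. I use 480 × 0.8 = 384 evaluable, 192 per arm.

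**2. How far NIHSS 0–1 depends on baseline.** Assume a normal change with SD 2.5 and a mean m that is the same at every baseline x. With integer scores, P(NIHSS ≤ 1 | x) = 1 − Φ((x − 1.5 − m)/2.5).

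| Baseline | PNS, m = 3 | Control, m = 2.1 |
|---|---|---|
| 4 | 1 − Φ(−0.20) = 57.9% | 1 − Φ(0.16) = 43.6% |
| 8 | 1 − Φ(1.40) = 8.1% | 1 − Φ(1.76) = 3.9% |
| 12 | 1 − Φ(3.00) = 0.1% | 1 − Φ(3.36) = 0.04% |

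The gradient is steep, but it rests on the equal-improvement assumption. Suppose instead that improvement is proportional to baseline, with the same average at a mean of 8. A PNS patient at 4 then improves by 3 × 4/8 = 1.5 on average, giving 1 − Φ(0.40) = 34.5%. A control patient at 4 improves by 2.1 × 4/8 = 1.05, giving 1 − Φ(0.58) = 28.1%. The treatment difference at baseline 4 falls from 14.3 to 6.4 points, and that is where events are most likely.

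**3. Power for NIHSS 0–1, chi-square against logistic regression on baseline NIHSS.** Simulated with 192 per arm and 1,500 to 2,000 runs per setting; the Monte Carlo standard error is a little over 1 point per power. The baseline distribution is an assumption, because the document gives none.

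| Improvement | Assumed baseline mean | Chi-square | Adjusted |
|---|---|---|---|
| Same at all baselines | 6.9 | 50% | 61% |
| Same at all baselines | 7.7 | 43% | 52% |
| Same at all baselines | 7.9 (SD 2.9) | 41% | 49% |
| Same at all baselines | 9.2 | 28% | 33% |

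With equal improvement the gain is typically 7 to 9 points; single settings ran from about 4 to 11. In the 7.9 row the event rates are about 19% against 12.5%.

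With proportional improvement, five assumed baseline distributions gave 24.7% to 25.6%, 22.3% to 24.0%, 53.4% to 54.7%, 50.5% to 50.9% and 10.6% to 8.8%. The gain is about 1 to 2 points at best, and in one setting it was slightly negative.

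**4. Other binary outcomes (mRS, BI).** The document gives no event rates and no correlation with severity, so both are assumed. For 40% against 54%, power goes from about 78% to 79% if baseline NIHSS predicts the outcome with AUC 0.58, to 84% at AUC 0.71, and to 91% at AUC 0.80. For 20% against 32.5%, it goes from about 80% to 84% at AUC 0.70 and 88% at AUC 0.78.

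**5. Biomarkers.** With equal variance σ² at both visits and correlation r, a change score has variance 2σ²(1 − r) and ANCOVA on the own baseline has σ²(1 − r²). The ratio is (1 + r)/2: 0.65 at r = 0.3, 0.75 at r = 0.5, 0.85 at r = 0.7. The value of r is not given.

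**6. PRO-Stroke and SS-QOL on baseline NIHSS.** The variance factor is 1 − r². From 80% unadjusted power this gives 80.4% at r = 0.1, 83.6% at r = 0.3 and 89.9% at r = 0.5.

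**7. Validity.** With no treatment effect, the unadjusted test for generic binary outcomes rejected in 4.6% to 5.4% of runs.

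**The case against.** The best case for the plan is that nothing in it is wrong. Each outcome has a test that suits its type, the tests hold their level, no power is claimed outside the primary outcome, and a condensed article may leave supportive adjusted analyses to a fuller plan. Most of that stands. What it does not answer is that the article names a method for every outcome. The unadjusted test is a stated choice, and a more precise one is available from data already collected. An unshown plan may add adjusted analyses, but this document does not make them the main ones.

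A reader might infer three stronger things that the document does not support.

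- **That the unadjusted comparison is biased, with chance imbalance passing for an effect.** Under 1:1 randomisation such imbalance is already covered by the 5% level. The cost is precision.
- **That baseline severity largely determines all these outcomes.** The calculation shows this only for NIHSS 0–1, and only if improvement does not depend on baseline. It is plausible for mRS and BI but not quantified. Nothing supports it for PRO-Stroke, SS-QOL or the biomarkers, whose natural covariate is their own baseline level.
- **That the loss equals about 23% more patients.** That is ((1.96 − 0.035)/(1.96 − 0.228))² ≈ 1.23, for 41% against 48.6% power: one scenario, which nearly disappears under proportional improvement.

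It is also fair to object that the biomarker baselines are not ignored, since they enter by subtraction. That is right; the point is only that regression uses them better.

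**Conclusion.** The point holds as an efficiency improvement and no more. The planned tests for the binary secondary outcomes and the biomarkers are valid but leave collected baseline information unused, or used less well than it could be. For NIHSS 0–1 the price is about 7 to 9 points of power if improvement is unrelated to baseline severity, and about 1 to 2 points if it is proportional to it. Both rest on the planning means and SD, 192 evaluable per arm, and an assumed baseline mean of about 6.5 to 9.3. The document does not say which pattern of improvement holds. For mRS and BI the gain depends on an unstated predictive strength; for the biomarkers, on an unstated correlation. No figure in the protocol article becomes wrong.

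**What to change.** Before unblinding, pre-specify:

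- **NIHSS 0–1, mRS 0–1 and BI of 90 or more:** logistic regression with treatment, baseline NIHSS and centre. Report the standardised (marginal) risk difference with 95% CI, tabulate the raw proportions beside it, and keep chi-square or Fisher as a sensitivity analysis.
- **ICAM-1, IL-6, TNF-α and MMP-9:** for each, ANCOVA on the log day-10 level with its own log baseline level and centre.
- **PRO-Stroke and SS-QOL:** adjustment for baseline NIHSS is optional.

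The plan should also say how small centres are handled. There are 11 hospitals, and at the rates in the 7.9 row NIHSS 0–1 yields only about 192 × 0.19 + 192 × 0.125 ≈ 60 events. A simulation of a model of this kind, with age added as well, showed no loss of power.

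The cost is analysis-plan wording, modest programming and a little more explanation of model-based estimates; no new data are needed. For the binary outcomes and the two scales, little is gained where baseline NIHSS predicts the outcome weakly.

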### Subgroup Analyses

Subgroup analyses for the primary outcome will be performed according to the following baseline characteristics: age (> 65 years vs. ≤ 65 years); gender (female vs. male); symptom onset to randomization time (≤24 h vs. > 24 h); disease history of hypertension, diabetes mellitus, coronary heart disease, stroke, and hypercholesterolemia; smoking history; Trial of Org 10,172 in Acute Stroke Treatment classification; main arterial stenosis; and stroke severity based on the NIHSS score.

## Discussion

Given that only a minority of patients with non-minor AIS could benefit from revascularization treatment, there remains a need for safe pharmacological neuroprotection against brain tissue injury in AIS treatment. Previous unsuccessful translational research on neuroprotective agents with unimodal targets has indicated the need for a single medicine blocking different key AIS-related mechanisms based on the complex pathophysiological cascade events of AIS (Rogalewski et al., 2006). Preclinical studies have reported the positive effects of PNS in alleviating inflammation injuries, anti-oxidation, and anti-apoptosis (Wan et al., 2009; Chen et al., 2011; Wang et al., 2011; Chen et al., 2015; Huang et al., 2015; Shi et al., 2017; Fu et al., 2018; Meng et al., 2019; Wu et al., 2019a; Zhang et al., 2019). Notably, exploratory studies using neuroimaging examination as the surrogate endpoint have demonstrated the therapeutic effect of PNS (Gui et al., 2013; Ren et al., 2018). However, the precise effect of PNS on patients with AIS should be further assessed using clinical endpoints.

As one of the main considerations in a trial design, the selection of an appropriate primary outcome is largely dependent on the disease and should reflect the treatment effect and expected mechanism. In this EXPECT trial, the post-intervention neurological improvement according to the NIHSS score is the primary clinical endpoint. The short time-span between treatment and NIHSS assessment requires relatively less effort to trace patients meanwhile reducing the risk of loss to follow-up. Researchers performed a causal mediation model using combined data from the MR CLEAN trial and IMS III trial and found that the change of NIHSS score reflected the treatment effect and lay on the causal pathway between treatment and long-term mRS categories. The results suggested that the NIHSS measures both neurological deficits and functional outcomes and that it could act as an alternative primary outcome for AIS treatment trials (Chalos et al., 2020).

To our knowledge, the EXPECT trial is the first multicenter, randomized, double-blind, placebo-controlled trial to assess the efficacy and safety of PNS in patients with AIS in the reperfusion era. This study is limited in terms of the lack of imaging assessment in follow-up procedures as unfavorable outcome predictors due to inadequate funding. However, we will explore the therapeutic mechanism of PNS therapy in the alleviation of cerebral ischemia-induced inflammatory damage. Moreover, the results will be valuable to interpret the efficacy of PNS. In summary, the EXPECT trial will provide critical evidence for PNS therapy for the vast majority of patients with AIS who are ineligible or have missed the opportunity for revascularization treatment.
